# 3.4 Mortality Survey

### 3.4.1 Methods

The second method of the cost-effectiveness analysis will be a compare the incremental cost estimates described above with mortality data. IDCAP has contracted with the Uganda Bureau of Statistics (UBOS) to measure the impact of the IDCAP intervention on mortality rate among children under five (U5) who live within the 5km radius of each of the 36 health facilities where IDCAP is operating countrywide. The mortality rate is the ratio of the number of deaths among children U5 to the total number of children U5 during a 12 month period. The impact will be measured as the “difference in differences,” i.e. the difference in the mortality rate at 18 phase 1 sites (intervention) compared to the difference at 18 phase 2 sites (control), where the difference in the mortality rate is the average baseline mortality rate minus the mortality rate during Phase 1. A comparison of the difference in mortality in phase 1 sites to phase 2 sites will provide an alternative estimate of the incremental benefit (i.e. B3 of Table 2). The incremental cost effectiveness ratio will be estimated as the ratio of the incremental cost (i.e. B4 of Table 2) to the difference-in-difference in mortality between phase 1 and phase 2 sites.

A 3-year recall period is set for this survey i.e. from April 2008 to the present, including 1.5 or 2 years of baseline data (April 2008-March 2010), and 12 or 18 months of data after the intervention began (April 2010 to September 2011).

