### 3.4.2 Design

For the second cost-effectiveness analysis, an alternative measure of effectiveness will be years of life saved. Population-level data is the only valid way to directly measure the effect of the intervention on health outcomes.

It is expected that the capacity-building and quality improvement interventions will reduce mortality by improving the emergency triage and treatment of patients and improving the quality of care for infectious diseases. The Uganda Child Verbal Autopsy Study showed that 75% of children who died received care from a government or private hospital or health center.[[35]](#endnote-36) Given that these children had access to care, it may be possible to save their lives by improving the quality of that care.

When the quality of care improves, utilization of a health facility increases.[[36]](#endnote-37) [[37]](#endnote-38) If the quality of care improves at the Phase 1 sites, they are likely to attract more patients including sicker patients. Paradoxically, as the quality improves the mortality of patients at the facility may increase, because the volume of patients and case complexity increases. Population-level data at the Phase 1 sites would reveal that population-level mortality had decreased because more people are seeking care, even if facility-level mortality increased.

UBOS proposed estimating population-level mortality with a two-part sampling method that builds on recent advances in the Demographic Surveillance Systems in which representatives of local council members at the parish level provide information about recent deaths. Although vital records systems may not be reliable in many African countries, there is a policy in Uganda for citizens to report births and deaths to the local council members. The information is more reliable in rural parishes than urban.

In the first part, the local council member directs the interviewers to households where there is a “high index of suspicion” that a death of a child U5 has occurred. To ensure completeness, a listing of households in each enumeration area (EA) would be created from interviews with all households in collaboration with the local council member. The listing includes an identification number and location for each household, whether or not a death occurred within the household in the last 3 years, and if yes, the age of the person at the time of his/her death.

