Households will be selected from 2 strata/tiers for household and birth history interviews.

1. 100% of all households that report a child who was less than five years at the time of his/her death died in the last three years. We expect an average of 4.2 deaths per EA (.028 mortality rate * 150 households/EA * 1 child/household) per year, or 12.6 in 3 years.  Some EA will have more households in the numerator and some will have less.
2. A random sample of 30 households. (See section 3.4.4 below). On average 2.5 household with a death will be among the 30 households selected at random to calculate the denominator.  (30 household in sample/150 household in EA = 0.2 probability of selected at random.  12.6 households in numerator * 0.2=2.5 households.)    We would have their information from strata/tier 1, and they would not need to be re-interviewed in stata/tier 2. On average, this would bring the number of new interviews for strata/tier 2 down to 28 instead of 30. Some EA will have more new interviews for strata/tier 2 and some will have less. Conservatively, we should continue to plan on conducting interviews with 30 household in strata/tier 2.

The IDCAP mortality survey differs from DHS, because we are interested in exposure to the IDCAP intervention, i.e. the length of time that people live within 5 km of the IDCAP site. The following information is needed on each member of the household: a)birth date (age), b) link to “natural” mother, i.e. is birth mother included in household listing**,** c)exposure, i.e. number of months living in household or EA **,** d) Vital status i.e. alive or dead, e) if death, date of death and residence on date of death.

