### 3.4.6 Limitations

One limitation is the length of time during which mortality will be observed. Some researchers recommend observing mortality over a 2 year period, because of fluctuation in yearly rates. It will only be possible to observe mortality over a maximum of 18 months, because the duration of the on-site support in Phase 1 will be total of 18 months. It will be possible to observe mortality at baseline over two years.

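### The mortality survey looks back three years for child deaths, but the periods it is to compare are printed as 42 months; the recall rule, baseline and expected counts need one start date

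*Protocol*

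**What the plan says.** Section 3.4.1 defines the recall period: "A 3-year recall period is set for this survey i.e. from April 2008 to the present, including 1.5 or 2 years of baseline data". The dates attached to the two periods are "April 2008-March 2010), and 12 or 18 months of data after the intervention began (April 2010 to September 2011". The effect is a difference in differences between the 18 Phase 1 and 18 Phase 2 sites, in which "the difference in the mortality rate is the average baseline mortality rate minus the mortality rate during Phase 1".

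Section 3.4.2 gives the rules that interviewers would follow. The listing of all households in an EA records "whether or not a death occurred within the household in the last 3 years". The first stratum takes all households reporting a child who was "less than five years at the time of his/her death died in the last three years". The expected yield is set there too: "We expect an average of 4.2 deaths per EA" per year, or 12.6 over three years.

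Section 3.4.4 makes it a design feature that every under-five death in the EA during the period of interest is found. It plans 300 EAs per arm, with household and birth history interviews in 12,600 households per arm.

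Section 3.4.6 allows up to 18 months of observation after the intervention starts and adds: "It will be possible to observe mortality at baseline over two years".

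**The concern.** The period to be analysed and the window in which deaths are sought are not the same length. Sections 3.4.1 (by its dates) and 3.4.6 (by its claims) describe 24 months before and up to 18 months after. The field rules and planned volumes describe 36 months counted back from the interview.

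This matters because the mismatch sits in data collection. A household whose only child death lies before the look-back does not enter the first stratum. It can then appear only by chance, through the random sample of 30 of 150 households. Once the listing is done, analysis cannot recover those deaths. A window that moves with the interview date would also give different baseline months to sites visited at different times.

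**Working it through.** **Inputs from the protocol.** Baseline rate .028 per year, 150 households per EA, 1 child per household, 13% reduction (3.4.4); 30 households sampled per EA, selection probability 0.2 (3.4.2); 300 EAs and 12,600 interviews per arm (3.4.4). Interview dates are not given, so they are assumed below.

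**1. The plan's own counts.**
- Deaths per EA per year: .028 × 150 × 1 = 4.2. Over three years: 4.2 × 3 = 12.6. This reproduces the stated figure.
- Interviews per arm: 300 × (12 + 30) = 12,600, which also reproduces, with 12.6 taken as 12. Both figures rest on 36 months.

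**2. The printed periods.**
- April 2008 to March 2010 is 24 months and April 2010 to September 2011 is 18 months, so 42 in total.
- The either/or wording allows 18 + 12 = 30, 18 + 18 = 36, 24 + 12 = 36 or 24 + 18 = 42. Section 3.4.6 taken at its maximum is the last of these.
- At 42 months: 4.2 × 3.5 = 14.7 deaths per EA, and 300 × (14.7 + 30) = 13,410 interviews per arm.

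**3. Baseline months outside a literal 36-month look-back.** A 24-month baseline from April 2008 expects 8.4 deaths per EA. The last column assumes the denominator still counts 24 months.

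| Assumed interview date | Months lost | Deaths captured per EA | Loss | Rate read |
|---|---|---|---|---|
| End March 2011 | 0 | 8.4 | 0% | .028 |
| End September / start October 2011 | 6 | 6.3 | 25% | .021 |
| End November 2011 | 8 | 5.6 | 33% | .0187 |
| End March 2012 | 12 | 4.2 | 50% | .014 |

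For the second row, 300 × 2.1 = 630 deaths per arm fall outside the first stratum. If the 20% of those households caught by chance in the random sample were added unweighted, the rate would read .028 × (18 + 0.2 × 6) / 24 = .0224.

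**4. Effect on the comparison** (25% loss, 24-month denominator, 13% true reduction, no change in controls).
- Equal baselines of .028: the Phase 1 rate becomes .028 × .87 = .02436. The true within-arm change is .028 − .02436 = +.00364; it would read .021 − .02436 = −.00336, an apparent rise. The control change would read .021 − .028 = −.007. The difference in differences is −.00336 − (−.007) = .00364, unchanged.
- Unequal baselines, .030 in Phase 1 and .028 in Phase 2: true estimate .030 × .13 = .0039. Observed: (.0225 − .0261) − (.021 − .028) = .0034. A quarter of the .002 baseline gap is left unadjusted.
- With the arms reversed (.028 and .030), the estimate moves from .00364 to .00414.

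**5. Moving window.** Two sites with the same true rate, one interviewed at end September and one at end November 2011, would read .021 and .0187.

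**6. Power table.** With m = (1.96 + 0.84)² / ln(.87)² × [1/4.2 + 1/(4.2 × .87) + 2(1 − c/150)/c], the EAs per arm come to 282.7, 255.7, 242.2 and 228.7 for c = 10, 15, 20 and 30, against the stated 283, 256, 242 and 229. (Unrounded normal quantiles were used; two-sided .05 is assumed, as no alpha is stated for this survey.) The table rests on one year of deaths per arm, so the recall window does not enter it.

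**The case against.** The best defence is that section 3.4.1 is the only place that defines the recall period, and it names a calendar start, April 2008. If section 3.4.2 is shorthand for that definition, no deaths are lost. The either/or wording also admits two 36-month splits. Section 3.4.2 collects dates of death and months of exposure, so numerator and denominator could be cut to the same months. Finally, the outcome is a contrast between randomised arms, not a within-arm change.

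Much of this stands. It rules out two stronger readings that a reader might infer.

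- *The baseline rate will be understated and the effect estimate biased.* Understatement requires both a literal look-back and a denominator that counts the uncovered months, and the protocol says neither. With equal baselines the expected difference in differences does not move.
- *Residual baseline imbalance is large against the effect.* Taking the coefficient of variation of .25 in section 3.4.4 as between-site, with 18 sites per arm, gives an SD of .25 × .028 × √(2/18) = .00233. A quarter of that is .00058, or 16% of .00364. But that coefficient is between EAs: the standard cluster formula for rates, with EAs of 150 children as clusters, gives 258.8 and 307.7 EAs per arm at .25 and .35, matching the stated 260 and 310. With 300 independent EAs per arm the SD is .00057, and a quarter of it is about 4% of the effect. The protocol gives no between-site figure.

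The defence does not remove the inconsistency. The field rules do not carry the April 2008 anchor. Three years equals April 2008 to the present only for interviews at about the end of March 2011, before the printed follow-up ends. The 18 + 18 split fits only interviews at about the end of September 2011, and it contradicts the two-year baseline in section 3.4.6. The document is dated November 2011. That is not an interview date, and sections 3.0 and 3.4.1 differ on whether the survey is decided, so it shows only that later fieldwork is plausible. Trimming to covered months would work, but it is not stated and would also shorten the baseline.

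**Conclusion.** The point holds as an inconsistency in the data-collection rule. The printed periods total 42 months; the listing question, first-stratum rule, expected deaths and workload total 36. Followed literally, the rule conflicts with the condition in section 3.4.4 that all deaths in the period of interest are found.

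The size depends on the interview date: none of the 24 baseline months are lost at end March 2011, a quarter at the start of October 2011 and half at end March 2012. The reading of .021 (or .0224) additionally assumes an untrimmed denominator. The loss cancels in the expected difference in differences when true baselines and fieldwork timing are alike in the two arms. What remains at risk is the baseline level, the direction of the within-arm change, full adjustment for baseline differences, and comparability between sites interviewed at different times.

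**What to change.** Choose one of two routes before fieldwork.

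1. **Fixed start.** Put April 2008 into the listing question and the first-stratum rule for every household, whatever the interview date. Restate the expected deaths as about 14.7 per EA and the interviews as about 13,400 per arm. Cost: slightly longer recall and about 810 more interviews per arm (13,410 / 12,600, about 6% more; about 5% against the unrounded 300 × 42.6 = 12,780).
2. **Keep 36 months.** Start the baseline at the first month covered for the last household interviewed, and restrict deaths and exposure to those months at all sites. Cost: a shorter baseline, for example 24 − 8 = 16 months if the last interview is at end November 2011.

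Under either route, make sections 3.4.1, 3.4.2, 3.4.4 and 3.4.6 state the same periods, and replace the either/or lengths in 3.4.1 with one baseline and one follow-up period.

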## 2.3 Research Question

Two sets of questions will be addressed.

1) Is an Integrated ID Training course (classroom and distance learning) for mid-level practitioners effective at building the skills required to perform key clinical tasks at acceptable standards? To answer this question, 2 mid-level practitioners from each of 36 sites will be invited to a Core Infectious Diseases course at IDI. The unit of analysis will be the individual. The evaluation design will be a before/after comparison of trainee skills and performance.

2) Does Onsite Multidisciplinary Team training and Continuous Quality Improvement activities, which is called On-Site Support (OSS), significantly improve clinic performance and health outcomes? If yes, are the OSS activities cost-effective? To answer these questions, 36 sites will receive the OSS activities for nine months, but 18 will be randomly assigned to receive the OSS in phase 1 and the others will receive it nine months later. The unit of analysis will be the site, and the evaluation design is a randomized trial of sites on key performance indicators.

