### Specific objectives

1. Evaluate the effectiveness of the integrated Infectious Disease Training in preparing mid-level practitioners to perform key clinical tasks corresponding to infectious disease competencies at acceptable standard
2. Evaluate the effectiveness of on-site support services (OSS) in improving clinic performance
3. Estimate the cost-effectiveness of site support services
4. Compare two methods for estimating cost-effectiveness: a) economic modeling in which effectiveness is measured by original data on performance indicators at 36 sites and published estimates of the effect of the performance indicators on Disability Adjusted Life Years (DALYS), and b) estimates in which effectiveness is measured original verbal autopsy data on mortality among children five years or less.
5. Evaluate the effectiveness of bi-monthly OSS for six months on clinical performance at Phase 1 sites after monthly OSS for nine months during Phase 1.

##

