# 3.3 Facility Cost and Performance Indicators

### 3.3.1 Methods

The second set of research question are: Does OSS, significantly improve clinic performance and health outcomes? If yes, are the OSS activities cost-effective? To answer these questions, 36 sites will receive the OSS activities for nine months, but 18 will be randomly assigned to receive the OSS in phase 1 and the others will be phase 2 sites that will serve as a control group in phase 1 and receive OSS months later. The unit of analysis will be the site, and the evaluation design is a randomized trial of sites on key performance indicators.

These research questions are reflected in specific objectives 2-5:

1. To evaluate the effectiveness of on-site support services in improving clinic performance
2. Estimate the cost-effectiveness of on-site support services
3. Compare two methods for estimating cost-effectiveness: a) economic modeling in which effectiveness is measured by original data on performance indicators at 36 sites and published estimates of the effect of the performance indicators on Disability Adjusted Life Years (DALYS), and b) estimates in which effectiveness is measured original verbal autopsy data on mortality among children five years or less.

5. Evaluate the effectiveness of bi-monthly OSS for six months on clinical performance at Phase 1 sites after monthly OSS for nine months during Phase 1.

For specific objectives 2 and 5, sites will be evaluated on the basis of a series of laboratory and clinical performance indicators for infectious diseases on the following areas: 1) preventing maternal to child transmission, 2) general HIV Care, 3) ART, 4) TB, 5) malaria, 6) emergency treatment and triage as presented in Table 1.

The laboratory performance indicators will be based on external quality assurance (EQA) data from three sources:

- National Tuberculosis Reference Laboratory data on acid-fast bacilli (AFB) smears for all IDCAP sites from Oct 2009 to present
- Uganda Virus Research Institute (UVRI) dry tube samples for HIV rapid test (3 positive and 3 negative per site) to test HIV panel proficiency
- Label and collect the 1st negative malaria blood smear and last positive smear each day for one month at every site.  Mobile team lab technicians will check the labels against the lab register to confirm they are the 1st negative and last positive.

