The exception is patients with HIV. The indicators on mortality for HIV patients will be measured from a cohort of patients who come for a visit during the first three months after the OSS begins. They will be exposed to the minimal risk of loss of confidentiality and asked to give verbal consent for IDCAP to follow their health status for 24 months. Contact information that is reported on HIV/ART cards will be collected. These patients will be asked to check with the evaluation clerk at the site each month when they come for a monitoring visit during treatment and report whether they are working and/or performing normal activities. At the end of phase 1 and 2, they will be offered a transportation refund for travel to the clinic for a total of two payments even if they complete or stop treatment. If the patient misses a monthly visit, the evaluation assistant will use the contact information to find out whether the patient has transferred out, stopped treatment, become bed-ridden or died.

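### The mortality comparison is given incompatible periods (9, 12 and 18 months), and the longer ones would count up to half of control time after control sites start OSS

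*Protocol*

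**What the plan says.** All references are to the Protocol.

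- Section 2.3 sets the stagger between arms: "18 will be randomly assigned to receive the OSS in phase 1 and the others will receive it nine months later".
- Section 3.3.1 limits the control role to that period: "the others will be phase 2 sites that will serve as a control group in phase 1".
- Specific objective 5 (section 2.4.2) gives the length of Phase 1 support: "at Phase 1 sites after monthly OSS for nine months during Phase 1". The Abstract and the hypotheses in section 2.5 also give nine months.
- Section 3.4.1 defines the mortality effect as a difference in differences, in which each arm's difference is "the average baseline mortality rate minus the mortality rate during Phase 1". The same paragraph defines the rate as deaths over children in a 12-month period.
- The next paragraph of 3.4.1, on the recall period, plans "12 or 18 months of data after the intervention began (April 2010 to September 2011".
- Section 3.4.6 explains the maximum of 18 months of observation by saying that "the duration of the on-site support in Phase 1 will be total of 18 months".
- Section 3.4.4 sizes the survey for 80% power to detect a 13% reduction from an annual rate of .028. Section 3.4.1 makes the mortality contrast the denominator of the second cost-effectiveness ratio.

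**The concern.** One contrast is given three lengths. If Phase 1 lasts nine months, the stated contrast has no control time on OSS, but it cannot supply a rate defined over 12 months. If the window is 12 or 18 months, its last 3 or 9 months compare sites on OSS with sites also on OSS. With Phase 1 support starting in April 2010, as 3.4.1 implies, Phase 2 sites would start about January 2011, well before the window closes in September 2011. The limitations in 3.4.6 do not mention this.

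A diluted contrast is pulled towards no effect. Because it is a denominator, dilution also raises the mortality-based cost-effectiveness ratio. That works against hypothesis 4b, which predicts that this ratio will be the lower of the two.

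**Working it through.** **Inputs.** Annual under-five mortality .028, a 13% reduction, 150 households per EA, one child per household, 80% power (section 3.4.4); 300 EAs per arm and between-EA coefficient of variation (CV) .25 or .35 (end of 3.4.4); control start at nine months (2.3). Alpha is stated only for the facility indicators (3.3.4). Two-sided .05 is assumed here and reproduces the plan's table.

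**Step 1. Reproduce the plan's figures.** On the log scale, with Poisson deaths and a denominator estimated from c sampled households:

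n per arm = (1.96 + 0.8416)² × (V0 + V1) / (ln 0.87)², where V = 1/(150 × rate × years) + (1/c)(1 − c/150).

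For c = 30 and one year:
- V0 = 1/4.2 + 0.0267 = 0.2648
- V1 = 1/3.654 + 0.0267 = 0.3003
- n = 7.849 × 0.5651 / 0.01939 = 228.7 (plan: 229)

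For c = 10, 15 and 20 the formula gives 282.7, 255.7 and 242.2 (plan: 283, 256, 242).

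With clustering, n = 1 + 7.849 × [(r0 + r1)/150 + k²(r0² + r1²)]/(r0 − r1)², where k is the CV, gives 258.8 (k = .25) and 307.7 (k = .35), against the plan's 260 and 310. The plan's numbers therefore rest on one full year of child-time with no control exposure.

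**Step 2. Share of control time on OSS.** 9 months: 0. 12 months: (12 − 9)/12 = 25%. 18 months: (18 − 9)/18 = 50%.

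**Step 3. Apparent effect,** assuming the full 13% reduction from the first OSS month in either arm:
- 12 months: the control rate becomes .028 × (1 − .13 × .25) = .02709. The reduction is 1 − .02436/.02709 = 10.1%; the absolute difference is 13% × .75 = 9.75% of the baseline rate.
- 18 months: the control rate becomes .028 × (1 − .13 × .5) = .02618. The reduction is 1 − .02436/.02618 = 6.95%; the absolute difference is 13% × .5 = 6.5% of the baseline rate.

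**Step 4. Power and size,** with c = 30, no clustering, and child-time equal to the window. Power at 300 EAs is Φ(|ln RR| / √((V0 + V1)/300) − 1.96).

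| Window | V0 + V1 | \|ln RR\| | Power at 300 EAs | EAs per arm for 80% |
|---|---|---|---|---|
| 9 months | 0.7357 | 0.1393 | 80% | 298 |
| 12 months | 0.5731 | 0.1062 | 68% | 399 |
| 18 months | 0.4055 | 0.0721 | 50% | 613 |

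One full year with no control exposure, as the plan assumes, gives 89% at 300 EAs. The longer windows add child-time but lose more through dilution.

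**Step 5. Nine months with clustering.** The cluster formula of step 1, with 150 × 0.75 child-years per EA, gives 328 EAs per arm (CV .25) and 377 (CV .35). Power at 300 is then 76% and 71%. Adding k² to each V in the log-scale formula gives 7.849 × 0.8607/0.01939 = 348 and 7.849 × 0.9807/0.01939 = 397. The requirement is thus roughly 330 to 400, against 300 planned.

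**The case against.** The strongest reply is that 12 or 18 months describes the recall period of the survey, not the analysis. The contrast is defined one paragraph earlier: "where the difference in the mortality rate is the average baseline mortality rate minus the mortality rate during Phase 1". With a nine-month Phase 1 and controls that serve only in Phase 1, no control time is on OSS. This stands in part. A reader might infer that the plan commits itself to a diluted comparison, and the documents do not support that.

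The reply does not settle the matter, because the mortality section does not keep to nine months. Section 3.4.6 gives Phase 1 support as 18 months and treats 18 months of observation as regrettably short, which suggests that all of it is to be used. Reading 18 months as all OSS at Phase 1 sites does not fit either: specific objective 5 gives nine plus six, or 15 months. A 12-month rate also cannot be formed from a nine-month Phase 1.

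Three other points for the plan hold:
- If the OSS effect builds up slowly, dilution is smaller than computed. A nine-month window would then also see less of the effect.
- The annual rate of .028 is not wrong for a shorter window, since it can be applied to child-time. The plan states no expected deaths for Phase 1 that could be called overstated.
- Mortality serves the comparison of cost-effectiveness methods, not the main test of facility performance, and section 3.0 still describes the survey as undecided.

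A reader might also infer that the HIV cohort, whose patients are "asked to give verbal consent for IDCAP to follow their health status for 24 months", has the same fault. That is not supported: no comparison between arms over 24 months is stated, and section 3.3.2 sets the performance-indicator comparison at month nine.

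**Conclusion.** The contradiction is firm: nine months, a 12-month rate, 12 or 18 months of data and an 18-month Phase 1 cannot all describe one contrast, and control time after OSS starts at Phase 2 sites is not dealt with. The dilution is conditional on the longer window being used, as 3.4.6 implies. In that case 25% or 50% of control time is on OSS, the 13% reduction appears as about 10.1% or 7.0%, and unclustered power at 300 EAs per arm is about 68% or 50%.

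These figures assume an equal and immediate effect in both arms, so under a lag they are upper figures for the loss. They also keep the plan's own simplifications: a comparison of two rates rather than a difference in differences, and the EA rather than the randomised site as the cluster. On the same basis the undiluted nine-month window has more power (80%) and no dilution, but less power than the 89% that the plan's one-year calculation gives at 300 EAs.

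**What to change.** 1. Reconcile sections 3.4.1 and 3.4.6 with the nine-month Phase 1 stated in the Abstract and sections 2.3, 2.4.2 and 2.5.
2. Define the primary mortality contrast by events rather than by a count of months: deaths per child-month from the start of OSS at Phase 1 sites to the day before OSS starts at Phase 2 sites, compared with the baseline rate per child-month. This replaces the 12-month ratio.
3. Report later months separately as a comparison of early with delayed OSS. The randomised arms still exist then, but the question is a different one.
4. Restate sample size and power for nine months of child-time: about 298 EAs per arm without clustering instead of 229, and roughly 330 to 400 with CV .25 to .35.

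**Cost.** No new data are needed, because section 3.4.2 already collects dates of death and months of exposure. The price is fewer deaths in the primary window and a less favourable stated power. At the baseline rate, 300 × 150 × .028 = 1,260 deaths per arm in a year become 1,260 × 0.75 = 945 in nine months. With clustering, 300 EAs per arm fall short of 80% power, so the sponsor must either add EAs or accept and state the lower figure. The shorter window also sharpens the concern in 3.4.6 about year-to-year fluctuation in mortality.
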